### Sample Size Estimation

Given the exploratory nature of this study, the sample size was not intended to provide a definitive or fully powered estimate of treatment efficacy. As no previous clinical trials have examined the effects of repeated sessions of TUS in patients with chronic pain, the sample size calculation was based on a prior clinical trial of rTMS for NP [8]. In that study, the mean reduction in pain score immediately after the final intervention was 34.8 (SD 15.2) in the active stimulation group (n=15). Assuming that the sham group would experience half of this effect (mean reduction of 17.4) [3,8] and that both active TUS groups in our study would yield the same mean reduction (34.8), the SD was set at 15.2 for all groups. On the basis of these assumptions, a one-way ANOVA with an α of .05 and 80% power indicated that 37 participants would provide a reasonable basis for estimating potential between-group differences. Accounting for a 5% dropout rate, the final target sample size was set at 39 (13 per group). The anticipated dropout rate of 5% was based on a previous rTMS trial conducted by our group in patients with NP, in which the dropout rate was below 5% [8].

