### Outcomes

#### Overview

The primary outcome is the change in weekly average pain intensity scores recorded in a pain diary using an 11-point NRS ranging from 0 (no pain) to 10 (worst imaginable pain). Participants will evaluate their average pain over the previous 24 hours daily at home. Weekly averages will be calculated, and changes from the baseline week to each postintervention week up to week 8 will be assessed. The primary end point is the change in weekly average pain scores from baseline to week 8. To assess clinically meaningful improvements, responder analyses will identify the proportion of participants achieving reductions of 2 points or more and 4 points or more [35] in weekly average pain scores at week 8 compared with baseline.

Secondary outcomes comprise patient-reported and physiological measures, enabling a multidimensional evaluation of pain, functional impact, psychological status, neurophysiological response, and patient perception over time. These include both longitudinal changes from baseline and postintervention assessments across the following domains.

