Demographic characteristics and outcomes will be summarized descriptively, with longitudinal outcomes presented as line graphs over time. The primary analysis will use a linear mixed-effects model for repeated measures (MMRM) to evaluate changes in weekly average pain scores from the pain diary. The model will include change from baseline in weekly average pain scores as the response variable, with treatment group, time point, and their interaction as fixed effects and individual participants as a random effect. Baseline pain scores will be included as covariates. The primary treatment effects will be estimated using model-based contrasts comparing M1 stimulation with sham stimulation and PSI stimulation with sham stimulation at week 8. Multiplicity arising from these 2 primary comparisons will be controlled using the Dunnett adjustment. To identify time points showing significant changes from baseline, the Dunnett multiple comparison procedure will be used, with the baseline week serving as the control. The number and proportion of responders will be summarized by treatment group, and between-group comparisons will be performed using logistic regression models adjusted for baseline pain scores. Missing week 8 pain diary data will be imputed using the last observation carried forward method for responder analyses only. Secondary outcomes measured repeatedly, such as pain NRS and SF-MPQ-2, will also be analyzed using MMRM in the same way as the primary outcomes. Outcomes assessed only at baseline and week 8—including BPI, EQ-5D-5L, HADS, PCS, PSEQ, MMSE, QST, and MEP—will be evaluated using analysis of covariance, with change from baseline as the response variable, treatment group as a fixed effect, and baseline value as a covariate. Paresthesia-related outcomes will be analyzed using MMRM, analysis of covariance, or logistic regression depending on data type and timing. PGIC responses at week 8 will be summarized by treatment group and compared using the Fisher exact test. All analyses will be 2 sided, with *P* values below .05 considered statistically significant.

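### Responder analysis: LOCF lets early leavers count as week-8 responders (a small expected effect), and the 4-point odds ratio may not be finite under standard maximum likelihood

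*Protocol article*

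**What the plan says.** The Outcomes overview of the protocol article defines responders by "reductions of 2 points or more and 4 points or more" in the weekly diary average, comparing week 8 with baseline, and offers this as the assessment of clinically meaningful improvement. Under Statistical Analysis, "between-group comparisons will be performed using logistic regression models adjusted for baseline pain scores". The missing-data rule for this analysis is: "Missing week 8 pain diary data will be imputed using the last observation carried forward method for responder analyses only".

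Four other statements bear on the point:

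- The full analysis set (Statistical Analysis) keeps any randomized participant with at least one session and one later outcome assessment, so early leavers stay in.
- The withdrawal criteria (Participants) include adverse events and withdrawn consent.
- Note a to Table 1 plans the week-8 evaluations even when the intervention has been discontinued.
- Sample Size Estimation plans 13 participants per arm and 5% dropout.

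**The concern.** The two parts are separate.

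**Carry-forward.** The outcome is status at week 8, but a participant whose last diary week was week 2 or 3 is judged on that week. If it was 2 points better than baseline, the participant is a success at week 8 whatever the reason for leaving. The primary MMRM does not fill the same gap in this way, and the article names no sensitivity analysis for the LOCF rule. The per-protocol set is defined by protocol deviations and does not test it.

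**Sparse responders.** With 13 per arm, a 4-point reduction under sham may be seen in nobody. A logistic model fitted by standard maximum likelihood then has no finite odds ratio. Sham is the common control, so both active-versus-sham odds ratios fail together. The comparison meant to show clinically meaningful benefit could end without a usable estimate, and a fallback chosen after seeing the empty cell would be data-driven.

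**Working it through.** **Inputs (Sample Size Estimation).** Mean reduction 34.8 in each active arm and 17.4 under sham; "the SD was set at 15.2 for all groups"; 5% dropout; 13 per arm.

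**The plan's own figure first.** The article states that "a one-way ANOVA with an α of .05 and 80% power indicated that 37 participants" would be a reasonable basis.

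- Grand mean = (34.8 + 34.8 + 17.4)/3 = 29.0, so deviations are 5.8, 5.8 and −11.6.
- Cohen's f = √[(33.64 + 33.64 + 134.56)/3]/15.2 = 8.20/15.2 = 0.540.
- Noncentral F power at α = .05 is 79.7% for N = 36 and 80.9% for N = 37.
- 37/0.95 = 38.9, hence 39. Both stated figures reproduce.

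**Responder rates.** The article does not give the scale of 34.8. Assume 0-100, so that on the 0-10 diary scale the means are 3.48 and 1.74 and the SD is 1.52. With normal changes, P(reduction ≥ c) = 1 − Φ((c − mean)/SD).

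| Threshold | Active | Sham |
|---|---|---|
| 2 points | 1 − Φ(−0.974) = 83.5% | 1 − Φ(0.171) = 43.2% |
| 4 points | 1 − Φ(0.342) = 36.6% | 1 − Φ(1.487) = 6.9% |

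**Size of the LOCF effect,** measured against counting missing as non-response, with 5% missing in every arm.

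- Expected number missing: 0.05 × 39 = 1.95, about 2. The chance of at least one is 1 − 0.95^39 = 86%.
- Upper bound, if every leaver's last diary week already shows the full planned effect:
  - 2 points: active 0.05 × 83.5 = 4.2 percentage points; sham 0.05 × 43.2 = 2.2; difference 2.0.
  - 4 points: active 0.05 × 36.6 = 1.8; sham 0.05 × 6.9 = 0.3; difference 1.5.
- One carried-forward responder moves an arm by 1/13 = 7.7 points; two in the same arm move it by 2/13 = 15.4.

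**Chance of an empty sham cell at 4 points.** P(0 of 13) = (1 − p)^13.

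| Sham rate p | P(0 of 13) |
|---|---|
| 5% | 51% |
| 6.9% (0-100 reading; unrounded 6.85%) | 39.7% |
| 10% | 25% |
| 15% | 12% |
| 20% | 5.5% |

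Expected sham responders at 6.85% are 13 × 0.0685 = 0.89. A simulation of 4,000 trials, including the baseline covariate (assumed normal, mean 6.5, SD 1.3, limited to 4-10), found no finite maximum-likelihood estimate in 40.4% at the 4-point threshold. If 34.8, 17.4 and 15.2 are instead read as percent reductions, with baselines of 5 to 8, P(0 of 13) is 81% to 100%.

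At the 2-point threshold (0-100 reading) the chance that some arm is all or none is about 18%, mainly an active arm in which everyone responds.

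**Does replacing LOCF cure the second problem?** No. With 5% of sham participants set to non-response, P(0 of 13) = (1 − 0.95 × 0.0685)^13 = 41.7%, against 39.7%. The two parts need separate remedies.

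**The case against.** **On LOCF.** The rule touches about two people in a supportive analysis of an exploratory trial. Note a to Table 1 means that stopping stimulation need not mean a missing week-8 evaluation. This stands, and it limits the size. It does not remove the problem: the note does not name the diary, and participants can leave the study altogether.

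A reader might take the 83.5% above as the chance that a week-2 or week-3 leaver in an active arm is scored as a responder. The document does not support that: the figure assumes the full end-of-treatment effect had already been reached, so it is an upper bound.

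Nor is the MMRM a standard that treats leavers as failures. It estimates week 8 as if they had continued like comparable participants. Counting missing as non-response answers a different question, and choosing it is partly a matter of estimand.

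**On the logistic model.** A reader might infer that the plan commits to ordinary maximum likelihood with Wald tests and that the 4-point comparison will often fail. The article says neither. It names only logistic regression, and penalised or exact fitting would be compatible with that; a statistical analysis plan not shown here may specify one. The planning figures come from a trial of a different stimulation technique, measured immediately after the last session and not as weekly diary averages. Their scale is unstated, and the sham value is itself assumed to be half the active one. The point is therefore conditional. The article also commits to reporting numbers and proportions of responders by group, so 0 of 13 would still be visible to readers.

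**Conclusion.** The point holds in limited form. The LOCF rule is stated, and it conflicts with a response defined at week 8. Its expected effect is at most about 4 percentage points in an active arm and 2 in the active-sham difference at the 2-point threshold. This assumes 5% dropout spread evenly across arms and the full planned effect in the last diary week; note a to Table 1 should reduce it further. A single participant still matters at 13 per arm.

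The sparse-data risk is potentially the larger of the two, but it depends on the fitting method and on the sham rate. Under standard maximum likelihood it is about 40% on the 0-100 reading, higher on a percent reading, and near 5% if the sham 4-point rate is 20%.

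It would be wrong to conclude that the trial's main result is at risk. The primary end point is analysed by the MMRM, which neither part affects.

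**What to change.** 1. Replace LOCF: count a participant without a week-8 diary average as a non-responder at both thresholds. As sensitivity, multiply impute the week-8 average from the weekly diary data and then apply the thresholds.
2. State that the responder models are fitted with Firth's penalised likelihood, adjusted for baseline pain. Report each active arm's risk difference against sham with a score-type interval (for example Miettinen-Nurminen).

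The cost is wording in the analysis plan, for which the article already provides an amendment route. Enrollment was at 20 of 39 on February 28, 2026, and investigators are not blinded, so the change should be fixed before outcomes by arm are examined.

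There are downsides. Response rates will be somewhat lower. Non-response for missing data is a composite estimand, and it is not necessarily conservative for the group difference: if more sham than active participants drop out, it favours the active arms. The multiple-imputation analysis is there to show whether this matters. The score-type risk differences are not adjusted for baseline pain, so they complement the adjusted model and do not replace it.

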#### Patient Global Impression of Change

This measure is administered at week 8, with participants rating overall perception of change on a 7-point Likert scale (“very much improved” to “very much worse”).

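### The 7-level ordered PGIC is compared with the Fisher exact test, which ignores the ordering, loses roughly 40-50% of a rank test's power at the planning effect, and gives no effect estimate against sham

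*Protocol article*

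**What the plan says.** The Outcomes section (Patient Global Impression of Change) defines the measure: "This measure is administered at week 8, with participants rating overall perception of change on a 7-point Likert scale". The levels run in order from the best to the worst judgement of change, and there is one rating per participant.

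The Statistical Analysis section gives the whole analysis in one sentence: "PGIC responses at week 8 will be summarized by treatment group and compared using the Fisher exact test". It also sets the sidedness for everything: "All analyses will be 2 sided". For PGIC it does not state a grouping of levels, a responder definition, or whether the test runs across three arms or between each active arm and sham.

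For other outcomes the same section is more specific. The primary outcome has model-based contrasts of each active arm with sham. The diary responder analyses have stated cut-offs (2 and 4 points) and logistic regression.

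**The concern.** The Fisher exact test on a table with more than two columns (the Freeman-Halton form) gives the same P value whatever order the columns are in. A consistent move towards improvement and a scatter across levels with no clinical direction therefore count alike. With seven columns and 13 people per arm, the test spreads its sensitivity over many patterns, few of which resemble a treatment benefit.

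It also returns only a P value. A proof-of-concept trial needs the direction and size of the difference from sham, with its uncertainty. What is at stake is the usefulness of one secondary outcome, the participant's own overall judgement.

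**Working it through.** **Inputs from the protocol article (Sample Size Estimation)**

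- Active arms: "the mean reduction in pain score immediately after the final intervention was 34.8 (SD 15.2) in the active stimulation group (n=15"); this is assumed for both, "both active TUS groups in our study would yield the same mean reduction (34.8), the SD was set at 15.2 for all groups".
- Sham: "Assuming that the sham group would experience half of this effect (mean reduction of 17.4").
- Design: "a one-way ANOVA with an α of .05 and 80% power indicated that 37 participants"; the target is 39, or 13 per group, after 5% dropout.

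**Step 1. Reproduce the plan's own figure.** Means 34.8, 34.8, 17.4; grand mean 29.0; deviations 5.8, 5.8, -11.6.

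- Variance of means = (33.64 + 33.64 + 134.56)/3 = 67.28.
- Cohen f = sqrt(67.28)/15.2 = 0.54.
- Noncentral F power: 0.797 at N = 36 and 0.809 at N = 37, so 37 is the smallest N that reaches 80%.
- 37/0.95 = 38.9, rounded up to 39.

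The stated sample size reproduces.

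**Step 2. Standardised effect.** (34.8 - 17.4)/15.2 = 1.145 SD for each active arm against sham.

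**Step 3. Carry the effect to PGIC.** The documents give no PGIC effect and no sham distribution, so both are assumed. A normal latent score, shifted in the active arms, is cut into seven levels. Four sham distributions were used (percent, worst to best level):

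- A: 2, 5, 10, 35, 28, 15, 5
- B: 1, 2, 7, 50, 30, 8, 2
- C: uniform
- D: 2, 6, 12, 40, 27, 10, 3

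Settings: 13 per arm, two-sided 0.05, permutation P values. Each cell has 1,500 simulated trials, so the Monte Carlo standard error is at most about sqrt(0.5 x 0.5/1500) = 1.3 points.

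**Step 4. Power at 1.145 SD in both active arms, three-arm test**

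| Sham distribution | Fisher, 7 levels | Kruskal-Wallis | Power lost |
|---|---|---|---|
| A | 43.1% | 77.5% | 1 - 43.1/77.5 = 44% |
| B | 47.0% | 77.6% | 1 - 47.0/77.6 = 39% |
| C | 47.6% | 77.9% | 1 - 47.6/77.9 = 39% |
| D | 38.5% | 78.3% | 1 - 38.5/78.3 = 51% |

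One active arm against sham: under A to C, Fisher has 41-46% and Wilcoxon 71-74%; under D, 41.7% and 74.9%.

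**Step 5. Smaller shifts, three-arm test**

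- 0.7 SD, D: 15.1% against 35.0%; loss 1 - 15.1/35.0 = 57%.
- 0.8 SD, A: 20.7% against 46.5%; loss 1 - 20.7/46.5 = 55%.
- 0.6 to 1.0 SD, A to C: Fisher keeps 0.44 to 0.55 of the rank test's power.

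**Step 6. Type I error.** With no effect, three-arm Fisher on seven levels rejected in 3.8-5.0% of trials and Kruskal-Wallis in 4.4-5.1%. The gap in power is not bought with a higher error rate.

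**Step 7. If a responder split was meant.** With the top two levels as response, three-arm Fisher has 57.3%, 46.5% and 57.2% power under A, B and C. The losses against Kruskal-Wallis are 1 - 57.3/77.5 = 26%, 1 - 46.5/77.6 = 40% and 1 - 57.2/77.9 = 27%. Under D, it has about 50-51%, a loss of about 35%.

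**The case against.** The strongest objection is that the article does not say a table of three arms by seven levels. Fisher on an improved/not improved split is an ordinary use of that test, and the definition may sit in a fuller document that is not shown. This stands as a limit on the size: under that reading the loss is about 26-40%. It does not remove the point, because the current text states no split, whereas the diary responder analyses do state their cut-offs.

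The inputs are also partly outside the documents. The 1.145 SD is a planning effect for pain, and a pure latent shift is the setting that suits rank tests. That stands too, so the figures are conditional. The ranking of the tests held for all four sham distributions and for shifts from 0.6 to 1.145 SD.

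Three stronger readings are tempting, and none is supported:

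- *That the test is invalid or the trial's main result is at risk.* Fisher controls type I error and suits sparse tables. PGIC is one of many secondary outcomes in a trial declared exploratory. The descriptive summary by arm is kept in any case.
- *That PGIC will most likely be reported as showing no difference even if stimulation works as assumed.* With 39-48% power, a null result is only modestly more likely than a positive one. At 0.7 SD the rank test, at 35%, would also usually miss.
- *That half the power is lost in every setting.* At the planning effect the loss is 39-51%, depending on the sham distribution, and it is smaller under a responder split.

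**Conclusion.** The point holds as one of efficiency and reporting. As written, the PGIC analysis discards ordering that the trial collects and provides no estimate against sham. If PGIC shifts by the 1.145 SD assumed for pain, Fisher on seven levels has about 39-48% power against about 78% for a rank test, so roughly 40-50% is lost; at smaller shifts the loss reaches about 55-58%. If an unstated responder split was intended, about 26-40% is still lost, and the cut-off then needs to be stated.

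These figures assume 13 evaluable participants per arm, a latent location shift, the sham distributions above, and that the pain effect carries over to PGIC. The primary mixed-model analysis and the sample size are unaffected.

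**What to change.** Replace the PGIC sentence in the Statistical Analysis section, and the matching text in the statistical analysis plan, so that it states:

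- Each active arm is compared with sham by a Wilcoxon-Mann-Whitney test or a proportional-odds model on the seven levels.
- The result is given as the probability of a better score, or the common odds ratio, with its confidence interval.
- The two comparisons are either labelled exploratory or adjusted for multiplicity.
- The frequency table by arm stays as description, and Fisher is used only for a responder split whose cut-off is fixed in advance.

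Adjustment for pain origin (central or peripheral), the randomisation stratum, is optional. It is sensible only if both strata are large enough, and the article gives no expected split. Neither the stratified analysis nor the proportional-odds model was simulated here; the power figures are for unstratified rank tests.

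The cost is wording only, with no new data and no change to visits or sample size. The article reports 20 of 39 participants enrolled by 28 February 2026 and provides for amending the analysis plan, so the change can be made and dated before the final analysis.

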### Patient and Public Involvement

Patients and members of the public will not be involved in the design, recruitment, or conduct of this study.

### Ethical Considerations

This study will be conducted in accordance with the ethical principles of the Declaration of Helsinki and the Clinical Trials Act of Japan. The study protocol was reviewed and approved by the University of Osaka Clinical Research Review Board (approval number S24007). All protocol amendments will be reviewed by the committee. Participants will be provided with detailed information about the study by the investigators, and written informed consent will be obtained before enrollment. Participation is voluntary, and consent may be withdrawn at any time. To protect confidentiality, each participant who provides informed consent will be assigned an identification code, ensuring that individuals cannot be directly identified. The correspondence table linking codes to personal information will be securely stored to prevent any disclosure of personal data outside the trial.

The clinical study report will be made publicly available via the Japan Registry of Clinical Trials website following review by the Clinical Research Review Board and the institutional administrator. Findings will also be disseminated through scientific presentations and peer-reviewed publications, with strict adherence to confidentiality.

### Protocol Amendments

During peer review of this protocol manuscript, the Statistical Analysis section was revised to explicitly specify the prespecified primary treatment comparisons (M1 stimulation vs sham stimulation and PSI stimulation vs sham stimulation at week 8) and the planned multiplicity adjustment.

## Results

The trial was registered in the Japan Registry of Clinical Trials on December 27, 2024 (jRCTs052240227). Enrollment began on April 30, 2025. As of February 28, 2026, a total of 20 participants had been enrolled, and enrollment is ongoing. Data collection is expected to be completed by December 31, 2027. The final analysis will be conducted after completion of follow-up and data verification.

## Discussion

This study has several notable strengths. First, to our knowledge, it is the first randomized, participant-blinded, placebo-controlled clinical trial designed to exploratorily evaluate the sustained effects of TUS in patients with NP. While previous TUS studies in pain have been limited to healthy participants or single-arm exploratory designs, this trial systematically examines the clinical effects of repeated sessions over an 8-week period. Previous TUS studies investigating pain have largely been conducted in healthy participants. For instance, TUS of the posterior insula has been reported to alter pain perception, whereas stimulation of other insular regions modulated autonomic responses such as heart rate variability, suggesting functional specialization within the insular cortex [11]. On the basis of these findings, PSI was selected as one of the stimulation targets in the present trial. In addition, another study demonstrated that MRI-guided TUS targeting the anterior thalamus altered pain thresholds in healthy adults in a sham-controlled design, further supporting the ability of TUS to modulate central pain-processing networks [12]. A preliminary clinical study has also investigated the use of TUS in patients with NP. Shin et al [13] conducted a prospective single-arm exploratory trial using navigation-guided TUS targeting the anterior cingulate cortex in 11 patients with chronic NP. They reported significant reductions in pain intensity along with improvements in pain-related interference with daily life. However, because the study was conducted without a control group and involved a small sample size, the ability to draw definitive conclusions regarding clinical efficacy remains limited [13].

Second, TUS is a novel noninvasive neuromodulation technique that enables precise targeting of both superficial and deep brain structures using a navigation system. Systematic reviews and meta-analyses suggest that rTMS targeting M1 produces analgesic effects in NP [3-5]. However, conventional rTMS primarily stimulates superficial cortical regions and may have limited efficacy when targeting deeper brain areas such as the M1 foot region [6-8]. To overcome this limitation, deep TMS using H-coil systems has been developed, allowing for stimulation of deeper brain regions. Nevertheless, H-coil stimulation typically generates a broader and less focal electric field, resulting in stronger stimulation of superficial areas and reduced spatial specificity [39]. In contrast, TUS enables relatively focal modulation of both superficial and deep brain structures [9].

This study also has several limitations. First, it is designed as an exploratory trial; therefore, it may be underpowered to detect subtle between-group differences. Second, the single-blind design, in which only participants are blinded, may introduce a potential risk of performance bias because operators cannot be blinded owing to technical constraints of the device. However, the primary outcome of this study is based on patients’ self-assessment of pain intensity, and participant blinding is considered the most critical factor in minimizing bias. Therefore, the validity of blinding for the primary outcome is considered reasonably assured. Nevertheless, residual bias related to the lack of investigator blinding cannot be completely excluded, particularly for secondary outcomes requiring investigator involvement. In addition, as a single-center study, the generalizability of the findings may be limited.

In conclusion, this trial represents, to our knowledge, the first randomized controlled trial to investigate the sustained therapeutic effects of repeated TUS in patients with NP. The findings are expected to provide exploratory proof-of-concept evidence regarding the safety and clinical efficacy of this TUS intervention.
